## Abstract

Early allograft dysfunction (EAD) is a functional hepatic insufficiency within a week of orthotopic liver transplantation (OLT) and is associated with morbidity and mortality. The etiology of EAD is multifactorial and largely driven by ischemia reperfusion injury (IRI), a phenomenon characterized by oxygen scarcity followed by paradoxical oxidative stress and inflammation. With the expanded use of marginal allografts more susceptible to IRI, the incidence of EAD may be increasing. This necessitates an in-depth understanding of the innate molecular mechanisms underlying EAD and interventions to mitigate its impact. Our central hypothesis is peri-reperfusion hyperoxemia and immune dysregulation exacerbate IRI and increase the risk of EAD. We will perform a pilot prospective single-center observational cohort study of 40 patients. The aims are to determine (1) the association between peri-reperfusion hyperoxemia and EAD and (2) whether peri-reperfusion perturbed cytokine, protein, and hypoxia inducible factor-1 alpha (HIF-1α) levels correlate with EAD after OLT. Inclusion criteria include age ≥ 18 years, liver failure, and donation after brain or circulatory death. Exclusion criteria include living donor donation, repeat OLT within a week of transplantation, multiple organ transplantation, and pregnancy. Partial pressure of arterial oxygen (PaO_2_) as the study measure allows for the examination of oxygen exposure within the confines of existing variability in anesthesiologist-administered fraction of inspired oxygen (FiO_2_) and the inclusion of patients with intrapulmonary shunting. The Olthoff et al. definition of EAD is the primary outcome. Secondary outcomes include postoperative acute kidney injury, pulmonary and biliary complications, surgical wound dehiscence and infection, and mortality. The goal of this study protocol is to identify EAD contributors that could be targeted to attenuate its impact and improve OLT outcomes. If validated, peri-reperfusion hyperoxemia and immune perturbations could be targeted via FiO_2_ titration to a goal PaO_2_ and/or administration of an immunomodulatory agent by the anesthesiologist intraoperatively.

## Introduction

### Early allograft dysfunction (EAD) impact and pathophysiology

Early allograft dysfunction (EAD) is a functional hepatic insufficiency within one week of orthotopic liver transplantation (OLT). Known risk factors for EAD are shown in “Table 1” [1].

**Table 1 pone.0301281.t001:** EAD risk factors by donor, procurement, and recipient characteristics.

Donor	Procurement	Recipient
Donor age > 45	Donors after circulatory death	Age
Steatosis > 30%	Prolonged ischemia time	MELD Score
		UNOS Status

^1^ Model for End-stage Liver Disease (MELD) score measures the severity of liver disease. United Network for Organ Sharing (UNOS) status is a numerical value used to assign relative priority for distributing donated organs.

EAD occurs in 20–25% of deceased donor OLT recipients and is associated with increased hospital costs, morbidity, and mortality [2–10]. The etiology of EAD is multifactorial, including donor and recipient factors, and largely driven by ischemia reperfusion injury (IRI). IRI is a process characterized by dysregulation of cellular oxygen homeostasis and innate immune defenses in the allograft after temporary cessation (ischemia) and later restoration (reperfusion) of oxygen-rich blood flow “Fig 1” [11, 12].

**Fig 1 pone.0301281.g001:**
[figure not shown]
Pathophysiology of hepatic ischemia reperfusion injury. ATP indicates adenosine triphosphate; ROS, reactive oxygen species; DAMPS, damage associated molecular patterns; NF-κB, nuclear factor-kappaB; MMPs, matrix metalloproteinases; NO, nitric oxide. Figure created with Biorender.com.

During the ischemia phase, oxygen deprivation causes reduced energy accessibility, inflammation, and hepatocellular swelling [10–14]. Decreased adenosine triphosphate (ATP) production leads to acidosis, cellular membrane ion pump dysfunction, excess intracellular calcium, mitochondrial fragility, sinusoidal constriction, and hepatocellular damage [11–14]. During the reperfusion phase, the reintroduction of oxygen elicits a self-perpetuating cascade of reactive oxygen species (ROS) and inflammatory cytokine production that leads to hepatocellular congestion, thrombus formation, and apoptosis [11–14].

The reperfusion phase occurs in two phases: (1) the initial phase, which occurs within the first 2 hours, and (2) the late phase, which occurs 6–48 hours after reperfusion [11, 12]. The initial phase of reperfusion is characterized by the release of ROS and proinflammatory cytokines [11–13, 15, 16] that upregulate adhesion molecules on the surface of hepatocytes and sinusoidal endothelial cells (SEC) [11, 12, 15]. In the late phase of reperfusion, neutrophils and T-cells bind to adhesion molecules on hepatocytes and SEC and infiltrate the liver parenchyma [1–12, 15, 17], leading to mitochondrial permeability and the release of damage-associated molecular patterns (DAMPS) [11, 12]. Through the release of DAMPS and activation of transcription factors, such as nuclear factor kappa-light-chain enhancer of activated B cell system (NF-κB), injured hepatocytes continue this self-perpetuating cycle of ROS and inflammatory cytokine production that ultimately leads to dysregulated microcirculatory blood flow, apoptosis, and coagulative necrosis [11, 12, 15–20].

### IRI as a critical barrier

To accommodate rising global demand for OLT in sicker patients and minimize death on the waitlist, the deceased donor pool has expanded with the use of extended criteria donors and marginal allografts more susceptible to IRI [21], including those with advanced age, donation after circulatory death (DCD), prolonged ischemia time, and steatosis. Hepatic IRI is a critical barrier to the current use and further expansion of the available deceased donor pool as the incidence of EAD and other poor postoperative outcomes may be increasing [22]. To mitigate the impact of IRI and EAD, normothermic regional perfusion (NRP) and hypothermic and normothermic machine perfusion have been implemented to restore allograft oxygenation pre-implantation. This new technology, however, has limited global accessibility and thus static cold storage of the allograft on ice remains the conventional and most widely used method of allograft storage worldwide.

### Effect of hyperoxemia on EAD

In a mouse model, postoperative hyperoxia with a fraction of inspired oxygen (FiO_2_) of 60% (equating to an average partial pressure of arterial oxygen or PaO_2_ of 230 mmHg) significantly increased IRI- induced hepatocellular damage compared to normoxia with a FiO_2_ of 21% [23]. In a human living donor liver transplantation (LDLT) study, intraoperative hyperoxia with a calculated average FiO_2_ ≥ 50% was associated with EAD and worse allograft survival compared to FiO_2_ < 50% [24].

There is no standard of care concerning the optimal peri-reperfusion oxygen level during OLT. Furthermore, the impact of peri-reperfusion excess oxygen exposure in deceased donor OLT recipients has not been examined. A 2022 expert panel of liver transplant clinicians recommended a restrictive oxygen strategy targeting a PaO_2_ of 70–120 mmHg during OLT, citing evidence from non-OLT surgeries such as abdominal surgery [25]. These abdominal surgery studies demonstrate an increased risk of mortality, cancer, atelectasis, and elevated cardiac injury markers with higher perioperative oxygen concentrations [25–29]. However, without evidence in deceased donor OLT, this recommendation has not been widely implemented. Many OLT anesthesiologists administer a high peri-reperfusion FiO_2_ to mitigate cellular hypoxia during malperfusion, while others administer a low FiO_2_ to attenuate IRI. We hypothesize peri-reperfusion hyperoxemia contributes to IRI and increases the risk of EAD. Examining this is important because variations in clinical practice may contribute to IRI and worse postoperative outcomes if excess oxygen exposure is associated with EAD.

### Novel serum biomarkers for EAD

Multiple studies demonstrate a distinct cytokine profile associated with IRI in OLT [11, 30, 31]. In a study measuring 38 cytokines in 53 OLT recipients, data suggest donors and recipients differentially contribute to cytokine expression in biopsy-proven IRI [30]. In this study, preoperative peripheral blood from recipients with IRI showed increased expression of tumor necrosis factor alpha (TNF-α), interleukin (IL)-5 (IL-5), IL-13, IL-2, IL-7, IL-8, and IL-1Ra [30]. Early in the postoperative period, patients who developed IRI demonstrated increased peripheral expression of IL-1Ra, IL-4, IL-13, and IL-17A [30]. Peripheral and portal IL-8 levels remained significantly elevated at all intraoperative time points tested [30] and could serve as a target for intervention [32, 33].

Furthermore, perioperative cytokine aberrations linked to IRI have been studied later in the development of EAD. One exploratory nested case-control study examined the pattern of expression of 25 serum cytokine levels in 73 deceased donor OLT recipients, 29 of whom developed EAD [34]. Serum samples were obtained preoperatively on the day of transplant and over 90 days postoperatively. The development of EAD was associated with lower IL-6 and higher IL-2R levels preoperatively [34]. The odds of developing EAD based on preoperative IL-6 and IL-2R levels in the multivariate model were 0.20 (95% CI, 0.06–0.64, p = 0.006) and 3.77 (95% CI, 1.22–11.64, p = 0.021) respectively [34], demonstrating the pre-transplant milieu may contribute to IRI and EAD. The development of EAD was also associated with higher MCP-1, IL-8, RANTES, MIG, IP-10, and IL-2R levels postoperatively, suggesting upregulation of the NF-κB pathway and T cell activation in the early postoperative period [34].

Though studies have associated peri-operative cytokine levels to IRI [11, 30, 31], there are limited data regarding the association of peri-reperfusion cytokine levels to EAD, particularly peri-reperfusion [35, 36]. We hypothesize perturbed cytokine, protein, and hypoxia inducible factor-1 alpha (HIF-1α) levels correlate with EAD. The identification of these aberrations may be used as novel biomarkers to assist in the development of new diagnostic approaches and therapeutic interventions for the identification, prevention, and management of EAD.

## Methods

### Study aims

Our central hypothesis is peri-reperfusion hyperoxemia and immune dysregulation exacerbate IRI and increase the risk of EAD. Our first aim is to determine the association between peri-reperfusion hyperoxemia and EAD after deceased donor OLT. We will examine peri-reperfusion median serum PaO_2_ levels to determine the odds EAD develops in patients exposed to hyperoxemia compared to those not exposed. Our second aim is to evaluate whether peri-reperfusion perturbed cytokine, protein, and HIF-1α levels correlate with EAD after OLT. We will measure peri-reperfusion serum cytokine, protein, and HIF-1α levels before and 2 and 48 hours after reperfusion for comparison between those who develop EAD and those who do not using the same participants from aim one. We will perform a subset analysis to determine whether peri-reperfusion hyperoxemia, compared to non-hyperoxemia, alters their pattern of expression.

### Design

This study is a pilot prospective single-center observational cohort study to determine (1) the association between peri-reperfusion hyperoxemia and EAD and (2) whether peri-reperfusion perturbed cytokine, protein, and HIF-1α levels correlate with EAD after deceased donor OLT. An observational design facilitates: (1) the examination of PaO_2_ within the confines of existing variability in anesthesiologist-administered peri-reperfusion FiO_2_, (2) prevents randomizing subjects to a potential harm, and (3) allows for the inclusion of patients with intrapulmonary shunting, which is common in patients with liver failure due to hepatopulmonary syndrome. This study does not meet criteria for a clinical trial per the National Institutes of Health (NIH) guidelines because it is observational and does not prospectively assign participants to an intervention to evaluate the effects of that intervention. A general study timeline is outlined in “Fig 2.”

**Fig 2 pone.0301281.g002:**
[figure not shown]
General study timeline. OLT indicates orthotopic liver transplantation; ICU, intensive care unit; SOC, standard of care; CBC, complete blood count; CMP, comprehensive metabolic panel; INR, international normalized ratio; ABG, arterial blood gas; AST, aspartate aminotransferase; ALT, alanine transaminase; EAD, early allograft dysfunction; AKI, acute kidney injury; PNA, pneumonia; CXR, chest x-ray; CT scan, computed tomography scan. Figure created with Biorender.com.

### Setting, key personnel, and facilities

This study will be performed at Emory University Hospital (EUH), a large academic hospital affiliated with Emory University School of Medicine in Atlanta, GA, USA. The principal investigator (PI) is a liver transplant anesthesiologist at EUH that will participate in and be responsible for the overall conduct of the study. The study team will consist of the PI, PI’s mentors, other liver transplant anesthesiologists and anesthesiology residents at our institution, laboratory technicians, and a study coordinator. All study team members will be certified to conduct research through the Collaborative Institutional Training Initiative (CITI) Program.

Biosample processing, immune assay batch analysis, and biosample long-term storage will occur in a laboratory at EUH. Immune assay kits will be purchased through Meso Scale Discovery, a division of Meso Scale Diagnostics LLC, Rockville, MD.

### Eligibility criteria

Inclusion criteria include age ≥ 18 years, end-stage liver disease, and donation after brain or circulatory death. Exclusion criteria include living donor donation, repeat OLT within a week of transplantation, multiple organ transplantation, and pregnancy or lactating patients. Eligibility criteria are summarized in “Table 2.” Prisoners do not meet criteria for OLT at our institution and are not included in this study. Donors after circulatory death who undergo NRP, a form of mechanical circulatory support similar to extracorporeal membrane oxygenation which restores oxygenated blood flow to the allograft after cardiac arrest and attenuates ischemic injury before recovery, will be included in the study. Patients who receive an allograft maintained on machine perfusion during storage, which re-exposes the allograft to oxygen before implantation, will also be included in the study. To limit the early re-exposure to oxygen as a confounding variable, these patients will be analyzed separately from those who receive an allograft maintained in static cold storage, the conventional method of allograft storage.

**Table 2 pone.0301281.t002:** Eligibility criteria.

Inclusion Criteria	Exclusion Criteria
Age ≥ 18 years	Living donor donation
End-stage liver disease	Repeat OLT within a week of transplantation
Donation after brain death	Multiple organ transplantation
Donation after circulatory death	Pregnancy or lactating patients

### Outcomes

The widely accepted Olthoff et al. definition of EAD is the primary outcome, specifically the presence of one or more of the following serum laboratory values: total bilirubin level ≥ 10 mg/dL on day 7, international normalized ratio (INR) level ≥ 1.6 on day 7, and peak aspartate transaminase (AST) or alanine transaminase (ALT) level > 2,000 IU/L within the first 7 postoperative days [1]. Secondary outcomes include: (1) the incidence and severity of postoperative acute kidney injury (AKI) as determined by the Kidney Disease Improving Global Outcomes (KDIGO) criteria, (2) number of postoperative days on mechanical ventilation, (3) evidence of postoperative pneumonia on chest x-ray or computed topography scan within the first 30 days postoperatively, (4) surgical wound dehiscence or infection within the first 30 days postoperatively, (5) anastomotic or non-anastomotic biliary strictures, biliary leak, bile duct stones or sludge, or ischemic cholangiopathy within the first 30 days postoperatively, (6) postoperative hepatic artery or portal vein thrombosis within the first 30 days postoperatively, and (7) 30-day all-cause mortality. Postoperative outcomes are summarized in “Table 3.”

**Table 3 pone.0301281.t003:** Primary and secondary outcomes.

Primary Outcome	Secondary Outcomes
EAD	Incidence and severity of postoperative AKI
	Number of postoperative days on mechanical ventilation
	Evidence of postoperative pneumonia on chest x-ray or computed topography scan within first 30 days postoperatively
	Surgical wound dehiscence/infection within first 30 days postoperatively
	Biliary complications within first 30 days postoperatively
	Postoperative hepatic artery or portal vein thrombosis within first 30 days postoperatively
	30-day all-cause mortality

IL-6, HO-1	Anti-inflammatory, reduces generation of ROS
HIF-1α	Hypoxia-signaling, regulates cytokine expression

[11, 30, 34, 37–40] IL indicates interleukin; TNFa, tumor necrosis factor alpha; IP-10, interferon gamma-induced protein 10; MIG, monokine induced by gamma interferon; MCP-1, monocyte chemoattractant protein-1; RANTES, regulated on activation, normal T cell expressed and secreted; PTX3, pentraxin-related protein 3; IFNg, interferon-gamma; HO-1, heme oxygenase-1; HIF-1a, hypoxia-inducible factor-1alpha.

### Sample size calculation

A total enrollment of 40 participants is planned. A post-hoc power analysis was performed based on exploratory data from Friedman et al. using the estimated mean and standard deviation (SD) of IL-8 on day 1 in the EAD and non-EAD groups to calculate effect size [34]. Since only median values and IQR were available, mean and SD of IL-8 for each group were estimated as median and IQR/1.35, respectively. A two tail post-hoc power analysis using an effect size of 0.717, alpha of 0.1, EAD sample size of 29, and non-EAD sample size of 44 achieved 84% power. To achieve power of 70% (A priori) with the same parameters, a total sample size of 40 is needed with at least 20 in each group. Given the pilot design of this study, a total sample size of 40 patients will be enrolled to generate preliminary data. This is feasible as our institution performs an average of 118 adult deceased donor OLT cases per year (Organ Procurement and Transplantation Network [OPTN], 2012–2021 data). Efforts will be made to enroll all eligible participants. There is no pre-determined percentage of subjects according to sex, gender, race, or ethnicity.

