### Statistical analysis

Patient and transplant characteristics will be reported descriptively (median and range or proportions). Patients will be grouped by the development of EAD or non-EAD. A type I error of 0.05 will be used as the criterion for statistical significance. Analyses will be performed using the R project for statistical computing.

For aim one, the proportion of patients exposed to hyperoxemia in each group, EAD or non-EAD, will be compared. Values will be presented as the median with interquartile range (IQR) or mean with standard deviation (SD) for continuous variables as appropriate and as the total number (percentage) for categorical variables. Comparisons between groups will be made using the Student’s t test or Mann-Whitney U test for continuous variables and chi-square test or Fisher’s exact test for categorical variables as appropriate. A multivariate logistic regression analysis will be performed with other EAD risk factors (e.g., donor type and age, ischemia time, and MELD score).

For aim two, cytokine, protein, and HIF-1α levels will be compared between the two groups, EAD and non-EAD, using analysis of variance (ANOVA) with Tukey’s adjustment for *p*-values at each time point and over multiple time points. For each biomarker, patients will be categorized into quartiles based on measured concentration, and the odds ratio for EAD will be compared among quartiles using a logistic regression analysis. The lowest quartile for proinflammatory cytokines (or highest quartile for anti-inflammatory cytokines) will be used as the reference group to calculate adjusted and unadjusted odds ratios for EAD. We will develop a logistic regression model of EAD as a function of inflammation, using the area under the receiver operating characteristic (ROC) curve and the Hosmer-Lemeshow goodness-of-fit test to assess model discrimination and calibration, respectively. We will perform a subset analysis to determine whether peri-reperfusion hyperoxemia, compared to non-hyperoxemia, alters their pattern of expression.

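### The sample-size paragraph mixes two alphas: 84% power reproduces only at 0.05 and 70% only at 0.10, and at the analysis alpha of 0.05 a 20/20 split has 60% power

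*Protocol article*

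**What the plan says.** The Sample size calculation section of the protocol article takes IL-8 on day 1 from a published nested case-control study and converts its summary statistics: "mean and SD of IL-8 for each group were estimated as median and IQR/1.35, respectively". It then makes two power statements.

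- For the published study's own group sizes: "A two tail post-hoc power analysis using an effect size of 0.717", with "alpha of 0.1, EAD sample size of 29, and non-EAD sample size of 44 achieved 84% power".
- For the present study: "To achieve power of 70% (A priori) with the same parameters", a total of 40 is required, with no fewer than 20 in each group.

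The Statistical analysis section sets a different significance level: "A type I error of 0.05 will be used as the criterion for statistical significance". The article gives no reason for sizing at 0.10 and testing at 0.05.

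**The concern.** The paragraph supplies every input needed to check its own figures: sidedness, effect size, alpha, group sizes and power. A reader who puts them in does not get 84%. The second sentence claims the same parameters, so both figures should follow from one alpha, and the testing alpha in the analysis section should match it.

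This calculation is the only quantitative support given for 40 patients. If the 70% holds only at an alpha that the analysis will not use, the study is credited with more power than it has. A null biomarker comparison would then be read against a claimed 70%, when the true figure under the plan's own significance rule is lower.

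**Working it through.** **Inputs, all from the Sample size calculation section unless noted**

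- Standardised difference d = 0.717, two-tailed test
- Stated sizing alpha 0.10
- Published study: 29 EAD, 44 non-EAD, stated power 84%
- Present study: 20 per group, stated power 70%
- Testing alpha 0.05 (Statistical analysis section)
- EAD incidence 20–25% (Introduction), used only in step 4

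The raw medians and IQRs behind d are not given, so d is taken as stated.

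**Method.** Pooled two-sample t test. The test statistic follows a noncentral t distribution with df = n1 + n2 − 2 and noncentrality λ = d × √(n1·n2/(n1 + n2)). Two-sided power is P(T > t_crit) + P(T < −t_crit).

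**Step 1: the 84% figure (29 versus 44).** λ = 0.717 × √(1276/73) = 0.717 × 4.181 = 2.998; df = 71.

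| Two-sided alpha | t_crit | Power |
|---|---|---|
| 0.10 (as stated) | 1.667 | 90.7% |
| 0.05 | 1.994 | 84.1% |

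Solving for the alpha that gives exactly 84% returns 0.0497. The stated figure is therefore the alpha 0.05 result, and it lies about 7 points below the correct value at its stated alpha.

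**Step 2: the 70% figure (20 versus 20).** λ = 0.717 × √(400/40) = 0.717 × 3.162 = 2.267; df = 38.

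| Two-sided alpha | t_crit | Power |
|---|---|---|
| 0.10 | 1.686 | 72.0% |
| 0.05 | 2.024 | 59.9% |

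At alpha 0.10, 19 per group gives 69.97%, so 20 is the smallest equal group size that reaches 70%. The total of 40 reproduces, but only at 0.10.

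**Step 3: size needed at the testing alpha.** At two-sided 0.05, 25 per group gives 69.99%. With 26 per group, λ = 0.717 × √13 = 2.585, df = 50, and power is 71.7%. So 70% takes 26 per group, 52 in total.

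**Step 4: the split the article itself leads one to expect.** At 20–25% incidence, 40 patients yield 8 to 10 EAD cases.

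| EAD / non-EAD | λ | Power at 0.05 | Power at 0.10 |
|---|---|---|---|
| 8 / 32 | 0.717 × √6.4 = 1.814 | 42.4% | 55.5% |
| 10 / 30 | 0.717 × √7.5 = 1.964 | 48.2% | 61.2% |

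**Step 5: could another calculation give 84% at alpha 0.10?**

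- *One-sided test.* It contradicts the stated two tails and does not help: 90.7% at one-sided 0.05, 95.5% at one-sided 0.10.
- *Mann-Whitney at two-sided 0.10.* With relative efficiency 3/π, 29/44 gives 89.5%; with the lower bound of 0.864, it gives 86.7%.
- *Welch test with unequal SDs.* With the EAD SD three to four times the non-EAD SD, 29/44 gives 85.9% to 85.3%. The article describes no such test, whereas the pooled test at 0.05 rounds to the stated figure.
- *A different effect size.* Forcing 84% needs d of about 0.637, and 20/20 at alpha 0.10 then gives only 63%.

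None of these reproduces both figures.

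**The case against.** The strongest reply accepts the arithmetic and disputes its weight. The 84% describes a past dataset and does not determine the sample size. The sentence that does determine it reproduces at its declared alpha of 0.10, and the 84% understates power at that alpha, so the error does not flatter the design. A relaxed alpha is a recognised choice for a pilot, the article declares it openly, and the Discussion says under both aims that the study may be underpowered. Reconciling the two sections could also mean adopting 0.10 in the analysis. The 52 depends on a strict threshold, because 25 per group already gives 69.99%.

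Much of this is fair. The total of 40 does follow from alpha 0.10, either alpha could be defended if used throughout, and 50 rather than 52 is arguable on rounding. What does not survive is the published text. The 84% is wrong at its stated alpha, the claim of unchanged parameters is false, and the 70% does not apply to tests judged at 0.05. A general caveat about low power corrects none of these.

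The expected EAD split is a separate weakness. It leaves power below 70% at either alpha, and this finding does not depend on it.

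**Conclusion.** The concern holds. No single alpha gives both power figures from the stated inputs: 84% belongs to two-sided 0.05, and 70% with 20 per group belongs to two-sided 0.10. At the 0.05 that the analysis will apply, 40 patients give 59.9% power for the assumed IL-8 difference, about 10 points short of the stated 70%. That is a best case, because it assumes an equal split; at the article's own incidence the figure is 42% to 48%.

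These results rest on d = 0.717 as stated, a pooled two-sample t test and a single comparison without multiplicity adjustment. The error concerns what is claimed for the sample size. It does not show that a pilot of 40 is unjustified.

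**What to change.** Rewrite the power statements in the Sample size calculation section on one alpha. Keeping 0.05 is simplest, since the Statistical analysis section already sets it. The corrected text would:

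- give 84% power for 29 versus 44 at two-sided 0.05;
- give 60% power for 20 versus 20 at two-sided 0.05, noting 72% at 0.10 for comparison;
- drop the claim that the two figures share the alpha of 0.10;
- add the power for 8 to 10 EAD cases among 40 on the same alpha (42% to 48%);
- rest the choice of 40 on the pilot purpose and feasibility, which the section already cites.

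If the investigators prefer 0.10 for the pilot, the Statistical analysis section must say so, and the 84% becomes 91%.

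The cost is one corrected paragraph and a lower stated power. Enrolment, endpoints and conduct are unaffected. The Procedures section reports 34 patients enrolled and no data analysed at publication, so at that point the correction could still be made before any results were seen.

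### The 70% power for 40 patients assumes 20 EAD cases and a 0.10 level; the protocol's own 20–25% incidence and 0.05 level give about 42–48%

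*Protocol article*

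**What the plan says.** All references are to the protocol article.

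- **Sample size calculation, size:** "A total enrollment of 40 participants is planned".
- **Sample size calculation, effect and alpha:** the effect size comes from IL-8 in an earlier study with 29 EAD and 44 non-EAD patients. The section reports "A two tail post-hoc power analysis using an effect size of 0.717, alpha of 0.1", and says this reached 84% power.
- **Sample size calculation, target:** "To achieve power of 70% (A priori) with the same parameters", it then says, "a total sample size of 40 is needed with at least 20 in each group".
- **Introduction, EAD impact and pathophysiology:** "EAD occurs in 20–25% of deceased donor OLT recipients".
- **Statistical analysis:** patients are grouped by whether EAD develops, and "A type I error of 0.05 will be used as the criterion for statistical significance".
- **Design and Sample size calculation:** this is a single-center observational cohort that tries to enroll every eligible patient. Nothing described enriches for EAD.
- **Discussion:** under each of the two aims, the authors say that the pilot may be underpowered. They give no figure.

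**The concern.** In a cohort, the sizes of the EAD and non-EAD groups follow from the incidence of the outcome; the investigators do not set them. A 20/20 split of 40 patients means 50% EAD, at least twice the incidence that the article gives. The 70% is also computed at a looser significance level than the one the analysis will use. Each fault overstates the power, and together they do so substantially.

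The Discussion says that trends in these data may shape a subsequent larger study. Planning from a power figure that this design does not have could mislead that work. At publication 34 patients were enrolled and no data had been analyzed, so the statement can still be corrected before results are read against it.

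**Working it through.** **Inputs.** From Sample size calculation: N = 40, d = 0.717, two-sided alpha 0.10, groups 20/20 (target 70%) and 29/44 (post-hoc 84%). From Statistical analysis: alpha 0.05. From the Introduction: EAD incidence 20–25%.

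**Formula.** Two-sample t test with n₁ + n₂ − 2 degrees of freedom and noncentrality δ = d·√(n₁n₂/(n₁+n₂)). Power is the probability that a noncentral t variable with that δ falls beyond ±t(1−α/2).

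**Step 1: reproduce the stated design.** For 20/20, δ = 0.717·√10 = 2.267. At alpha 0.10 the critical value is 1.686 and power is 72.0%. With 19/19 it is 69.97%, so 20 per group is the smallest equal size that reaches 70%. The stated N = 40 is right for its own inputs.

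**Step 2: change alpha only.** For 20/20 at 0.05 the critical value is 2.024 and power is 59.9%.

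**Step 3: change the split only.** The expected EAD count is 40 × 0.20 = 8 to 40 × 0.25 = 10.
- 8/32: δ = 0.717·√6.4 = 1.814
- 10/30: δ = 0.717·√7.5 = 1.964

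**Step 4: change both.** The results together:

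| Split (EAD/non-EAD) | alpha 0.10 | alpha 0.05 |
|---|---|---|
| 20/20 | 72.0% | 59.9% |
| 10/30 | 61.2% | 48.2% |
| 9/31 | 58.5% | 45.5% |
| 8/32 | 55.5% | 42.4% |

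Averaging over a binomial number of EAD cases, instead of fixing it at its expectation, gives 41% (20% incidence) and 47% (25%) at alpha 0.05.

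**Step 5: how likely are 20 EAD cases?** With X ~ Binomial(40, p), P(X ≥ 20) is 0.002% at p = 0.20 and 0.06% at p = 0.25.

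**Step 6: detectable effect.** Solving for the d that gives 70% power at two-sided 0.05 yields 0.93 SD for 10/30 and 1.01 SD for 8/32, against the 0.717 assumed.

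**Step 7: check the 84%.** For 29/44, δ = 0.717·√(29·44/73) = 2.998. Power is 90.7% at the stated alpha of 0.10 and 84.1% at 0.05. The 84% therefore matches 0.05, while the N = 40 figure matches 0.10. The two calculations do not share parameters as the text says.

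**The case against.** **The study is a pilot and says so.** N = 40 is justified by feasibility and preliminary data, and both limitation paragraphs warn of low power. This stands in part: it lowers the consequence and supports keeping N = 40. But the warnings carry no number and mention neither the split nor the alpha, so the quantified 70% remains in conflict with the rest of the article. A reader might infer that a null result would be taken as evidence at 70% power. Given those warnings, the documents do not support going that far.

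**The incidence is a literature range, and the article says EAD may be increasing.** True. At 40% EAD (16/24), power at alpha 0.10 is 70.4%. At the 0.05 that will be used it is 58.1%, and the chance of 20 or more cases is still only about 13%. Nor does the article state 40% as its expected incidence. That share is close to the 29 of 73 in the earlier study, which the article describes as a nested case-control study; such a fraction reflects sampling.

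**The condition of 20 per group is openly disclosed.** It is, and that disclosure should stay. What is missing is its reconciliation with the stated incidence.

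**Two further criticisms are tempting but are not errors here.**
- A reader might fault the lack of a power figure for the hyperoxemia aim. That is an omission in a condensed article, and any figure would need a proportion of hyperoxemic patients that the documents do not give.
- A reader might also object that day 1 IL-8 is not one of the sampled time points. Day 1 lies between the 2-hour and 48-hour samples, and using it as a planning proxy is a matter of wording.

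**Conclusion.** The concern holds as an internal contradiction. The N = 40 calculation is correct for its inputs, but two of those inputs conflict with the article's own incidence and significance level. Correcting either one alone leaves 55–61% power; correcting both leaves about 42–48%. Separately, the 84% post-hoc figure does not correspond to its stated alpha.

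The 42–48% assumes d = 0.717, all 40 patients in one comparison, and a single unadjusted two-group t test. It should not be read as the true power of the study. The plan covers 13 biomarkers at three time points with adjusted comparisons, and it analyzes recipients of NRP or machine-perfused grafts separately. It also says that those techniques are associated with less EAD. All of this would lower power further, by an amount the documents do not allow one to compute.

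**What to change.** Keep 40 patients as a pilot and revise the sample size section:

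1. Use the 0.05 level from the statistical analysis section.
2. Replace the 70% claim with the expected 8–10 EAD cases, power of about 42–48% at two-sided 0.05 for d = 0.717, and an effect detectable with 70% power of about 0.93–1.01 SD.
3. Keep the 20-per-group condition visible, and say that 70% would hold only with that split at alpha 0.10, which the stated incidence makes very unlikely.
4. Correct the 84% to about 91% at alpha 0.10, or relabel it as the alpha 0.05 result.
5. Add a sentence saying that the separate analysis of NRP and machine-perfusion recipients and the testing of 13 biomarkers reduce power further.

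The cost is wording only: no added patients or procedures, but a less favorable stated power.
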